### Strategies to improve adherence to interventions {11c}

The organizational support groups, composed of social workers and psychologists in shared accommodations, will encourage participants to use prevention materials. Due to their participatory development, these materials are more sensitive to language and culture. The organizational support groups are qualified for target group-specific, culturally sensitive language and are competent to use specific communication strategies to encourage participants.

### Relevant concomitant care permitted or prohibited during the trial {11d}

Concomitant care is permitted but is not foreseen during the trial.

### Provisions for post-trial care {30}

As the intervention implemented during this trial is a prevention concept and participants are free to participate, we do not expect that harm will occur to trial participants. Nonetheless, they can contact the research team until the project is finished at the end of March 2025.

### Outcomes {12}

The primary outcome is the increase of knowledge about substances, hazardous substance use, and induced health risks among refugees since baseline. This will be measured with the Drug and Drug Problems Perception Questionnaire (DDPPQ; [4] in an adapted version to test the efficacy of the prevention measures in providing health-related information creating a sum score for a continuous variable. Primary outcome will be measured at the study times t_0_–t_3_.

The following short-term secondary outcomes are assessed 9 weeks after the first implementation: health literacy measured with eHealth literacy scale (eHeals; (Norman et al. [24, 25]), attitudes towards substance use measured with an adapted version of the Substance Abuse Attitude Survey (SAAS; [8]), and the increase in knowledge of the workforce about substances, hazardous substance use, and health risks among refugees measured with an adapted version of the Drug and Drug Problems Perception Questionnaire (DDPPQ; [4]) related to the intervention.

In order to relate the outcomes directly to the intervention, the DDPPQ; [4] and the SAAS [8] were adapted to the intervention and the context of the concept implementation. As in other studies [9, 22], where the DDPPQ was also adapted to specific contexts, statements about the validity of the scales need to be tested in a context-specific way.

The following long-term secondary outcomes are assessed three months after first implementation: depression, anxiety, and stress measured with Depression Anxiety Stress Scale (DASS–21; [21]) and reduction of hazardous substance use measured with DSM-5 criteria of substance use disorder [5], Obsessive Compulsive Drug Use Scale-5 score (OCDUS-5; [13], 30-day prevalence of hazardous substance use, and a self-assessment of problematic substance use [33].

Control variables are socio-demographic data (e.g., age, gender, and nationality) and contextual factors (e.g., accommodation size).

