### Objectives {7}

The primary objective of this study is to evaluate the efficacy of a multi-component prevention concept for refugees in shared accommodations regarding refugees’ knowledge about hazardous substance use and induced health risks. It is hypothesized that their knowledge about the health system, addiction counselling, risks of hazardous substance use, and access to supportive structures increases in shared accommodations where the concept is implemented (intervention group) in comparison to the shared accommodations where the concept is not yet implemented (control group). The secondary objectives are to measure the impact of concept implementation on health literacy, attitudes towards substance use, hazardous substance use, depression, anxiety, and stress as well as the knowledge of the workforce about hazardous substance use and induced health risks.

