## Methods: participants, interventions, and outcomes

### Study setting {9}

The study will take place in nine shared accommodations in Stuttgart, Germany. The survey will consist of three clusters with three accommodations each. Using the web-based randomizing program random.org, shared accommodations are randomly assigned to each cluster. Implementation takes place in cluster A in weeks 1–3, cluster B in weeks 4–6, and cluster C in weeks 7–9. This results in five survey times t_0_–t_4_ (see Table 1): baseline, after implementation in clusters A, B, and C as well as the follow-up. In the study, data is collected and evaluated both at the level of the refugees and at the level of the qualification of the setting (qualification of the professionals in the shared accommodation, structural conditions of the setting). Qualified social workers or psychologists perform the implementation of the prevention concept.

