### Participant timeline {13}

Potential participants who reside in the selected shared accommodations will be invited to participate in the study after screening for eligibility. Information about the aims of the study and the possibility of asking questions will be provided by the research team and with multilingual information material. Further on, this material provides information about the funding, data management and protection, anonymization, confidentiality, estimated time to participate, incentives, freedom to withdraw at any time, and contact details. After giving informed consent, potential participants are invited to the baseline data collection (t_0_). Table 3. shows the detailed participant timeline. Baseline assessment will consist of sociodemographics, contextual factors, and primary and secondary outcomes (see outcomes). Afterwards, shared accommodations will be allocated into cluster A, B, or C. In cluster A, the intervention starts 1 week after baseline. According to the stepped-wedge design, implementation steps from one to another cluster take 3 weeks with an invitation to the participants for short assessments regarding primary and short-term secondary outcomes at the end of each implementation step (*t*_1_–*t*_3_). Ten weeks after baseline, the intervention ends in all clusters. Three months after baseline, participants are invited for follow-up to assess long-term secondary outcomes.

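### The long-term secondary outcomes are measured only before any accommodation has the concept and after all nine have had it, so its effect on them cannot be separated from time

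*Protocol article*

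**What the plan says.** The protocol article fixes the schedule for these outcomes in four places.

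- **Outcomes {12}:** "The following long-term secondary outcomes are assessed three months after first implementation". The list is DASS-21 depression, anxiety and stress, DSM-5 criteria, OCDUS-5, 30-day prevalence and a self-assessment of problematic use.
- **Participant timeline {13}, baseline:** "Baseline assessment will consist of sociodemographics, contextual factors, and primary and secondary outcomes (see outcomes". Allocation follows this survey.
- **Participant timeline {13}, later surveys:** t1 to t3 are "short assessments regarding primary and short-term secondary outcomes at the end of each implementation step". The long-term outcomes return once: "Three months after baseline, participants are invited for follow-up to assess long-term secondary outcomes".
- **Roll-out:** Study setting {9} says "Implementation takes place in cluster A in weeks 1–3, cluster B in weeks 4–6, and cluster C in weeks 7–9", and Participant timeline {13} adds "Ten weeks after baseline, the intervention ends in all clusters". The five survey times are "baseline, after implementation in clusters A, B, and C as well as the follow-up".

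The comparator section {6b} defines control as accommodations still waiting for the concept. Objectives {7} states: "The secondary objectives are to measure the impact of concept implementation on health literacy", and the same sentence goes on to hazardous substance use, depression, anxiety and stress. Statistical methods {20a} assigns multilevel linear or logistic regression to the short-term and long-term secondary outcomes alike.

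**The concern.** A stepped-wedge trial separates the intervention from the passage of time because, at some surveys, some clusters are treated while others still wait. For the long-term outcomes no such survey exists. The data form a before-after comparison in nine accommodations, yet the objective and the analysis section treat them as if they carried the stepped-wedge contrast.

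These are all of the trial's mental-health and substance-use outcomes. Any change over about three months from season, time since arrival, repeated questioning or selective dropout would be reported as an effect of the concept, in either direction.

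**Working it through.** **1. Exposure at each measurement.** Take three months as about 13 weeks. Cluster A starts one week after baseline, B three weeks after A, and C six weeks after A. Roll-out ends at 1 + 9 = 10 weeks after baseline, as the protocol says.

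| Survey | Long-term outcomes taken? | Accommodations with the concept |
|---|---|---|
| t0 | yes | 0 of 9 |
| t1 | no | 3 of 9 |
| t2 | no | 6 of 9 |
| t3 | no | 9 of 9 |
| t4 | yes | 9 of 9 |

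If t4 is dated from baseline it falls at about week 13. If it is dated from first implementation, it falls at about week 14. Both come after week 10, so the table holds under either anchor.

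**2. Identifiability.** Write the model as period effects plus a treatment indicator, and compare the rank of the design matrix with its number of columns.

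- Surveys t0 and t4: 3 columns, rank 2. The treatment column equals the t4 column. With nine accommodation effects added it is 11 columns, rank 10.
- Surveys t0 to t3 (primary outcome): 5 columns, rank 5, identified.
- Surveys t0 to t4, had the long-term outcomes been taken at all five: 6 columns, rank 6, identified.

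**3. What happens if the time term is left out.** The model then fits, but it estimates effect plus trend. A simulation with a true effect of zero shows the size. It assumes 9 accommodations of 28, SD 1, ICC 0.01 and within-person correlation 0.5, with a t-test on the nine accommodation mean changes and 2,000 runs.

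| Assumed background trend (SD) | Mean estimate (SD) | Rejections at two-sided 5% |
|---|---|---|
| 0 | 0.00 | 5% |
| 0.1 | 0.10 | 29% |
| 0.2 | 0.20 | 79% |
| 0.3 | 0.30 | 99% |

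The trend sizes are illustrative; the protocol gives none.

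**4. The randomised contrast that remains.** At t4 the sequences differ in time since start: about 12, 9 and 6 weeks under the baseline anchor, or 13, 10 and 7 under the other. A and C differ by 6 weeks either way.

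Inputs from Sample size {14}: ICC 0.01 and 28 per accommodation (9 × 28 = 252, as stated). Each sequence has 3 accommodations, so 84 participants. Assumed: SD 1, no dropout, and baseline adjustment that reduces the whole variance by 1 − r².

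- Variance of A − C = 2 × (0.01 + 0.99/28)/3 × (1 − r²) = 0.0302 × (1 − r²)
- SE = 0.174 at r = 0, and 0.174 × √(1 − 0.49) = 0.124 at r = 0.7
- Six accommodations give 6 − 2 = 4 degrees of freedom. The multiplier for 80% power at two-sided 5% is 2.776 + 0.941 = 3.72.
- Detectable difference = 3.72 × 0.174 = 0.65 SD at r = 0, and 3.72 × 0.124 = 0.46 SD at r = 0.7

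The normal multiplier of 2.8 would give 0.49 and 0.35 SD, which is too optimistic with six accommodations. Pooling the variance over all nine would add two degrees of freedom and help a little; dropout or a higher ICC would hurt. The figures apply to the continuous scales only.

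**The case against.** - **Not everything is lost at t4.** Time since implementation differs between sequences by randomisation, and the Discussion says that differences in how long the concept has been in place can be analysed. This stands. A model with period effects and a linear exposure-time term through zero has full rank (3 of 3). But it gets from earlier-versus-later to concept-versus-none only by assuming that shape; with a treatment indicator and exposure time together the rank is 3 of 4. The Discussion does not present duration as the analysis of the long-term outcomes.
- **The analysis plan is not shown.** The article does not state period effects or how exposure is coded, and it may leave both to that plan. This is fair as to the model, but the problem lies in the survey schedule. No model supplies an untreated accommodation at t4.
- **Tables 1 and 3 are not shown.** The text still says explicitly which outcomes are taken at which survey.
- **Only secondary outcomes are involved.** Correct. The stated hypothesis and the trial's main aim concern knowledge, which is unaffected.
- **Stronger readings that a reader might infer.** One is that listing *reduction* of hazardous use among the outcomes is already a claim of effect. It reads more naturally as a change outcome, parallel to the increase in knowledge; the word at issue is *impact* in the objectives. Another is that regression to the mean must inflate the change. The eligibility criteria do not select for high distress or use, and they exclude acute crises, so this has little support.

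**Conclusion.** The point holds for the long-term secondary outcomes. As scheduled, the effect of the concept versus no concept on DASS-21, DSM-5 criteria, OCDUS-5, 30-day prevalence and self-assessed problematic use is confounded with calendar time. This needs no numerical assumption beyond t4 falling after roll-out ends, which is true under both anchors.

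A reader might infer that the trial as a whole is confounded, or that nothing randomised is left for these outcomes. The documents support neither: the primary outcome is identified from t0 to t3, and the sequences can be compared at t4. That comparison is imprecise and answers a different question, namely earlier against later implementation. Its 0.46 to 0.65 SD rests on carrying the sample-size ICC of 0.01 over to other outcomes and on the further assumptions listed in the working.

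The two datings of t4 are a separate, minor inconsistency of about one week. They should be reconciled but do not change the conclusion.

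**What to change.** 1. In Objectives {7}, Outcomes {12} and Statistical methods {20a}, state that t0–t4 changes in these outcomes are descriptive before-after results, and withdraw the aim of measuring the concept's impact on them through the stepped-wedge comparison.
2. In Statistical methods {20a}, name the baseline-adjusted comparison of sequences A, B and C at t4 as their only randomised analysis, describe it as earlier versus later implementation, and note its low precision.
3. Use one anchor for t4 in Outcomes {12} and Participant timeline {13}.

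The cost is wording and a weaker claim. No new data are needed, which matters because the trial status section has data collection ending in 10/2024.

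Adding a 30-day-use item at t1 and t2 is not recommended. Its recall window is longer than the three-week step, so answers would mix time before and after implementation.

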### Participant timeline {13}

Potential participants who reside in the selected shared accommodations will be invited to participate in the study after screening for eligibility. Information about the aims of the study and the possibility of asking questions will be provided by the research team and with multilingual information material. Further on, this material provides information about the funding, data management and protection, anonymization, confidentiality, estimated time to participate, incentives, freedom to withdraw at any time, and contact details. After giving informed consent, potential participants are invited to the baseline data collection (t_0_). Table 3. shows the detailed participant timeline. Baseline assessment will consist of sociodemographics, contextual factors, and primary and secondary outcomes (see outcomes). Afterwards, shared accommodations will be allocated into cluster A, B, or C. In cluster A, the intervention starts 1 week after baseline. According to the stepped-wedge design, implementation steps from one to another cluster take 3 weeks with an invitation to the participants for short assessments regarding primary and short-term secondary outcomes at the end of each implementation step (*t*_1_–*t*_3_). Ten weeks after baseline, the intervention ends in all clusters. Three months after baseline, participants are invited for follow-up to assess long-term secondary outcomes.

**Table 3. Tab3:**
[figure not shown]
Participant timeline

### Sample size {14}

Following the recommendation of Ouyang et al. [27], the calculation of the estimated number of participants is based on Hemming et al. [16]. Using the described trial design as a stepped-wedge design with a cohort sample structure and an exchangeable correlation structure, we allow varying cluster sizes. According to our experiences with previous research in this field, we assume a coefficient of variation of cluster sizes of 10 participants, mean difference of 0.15, and an intra-class correlation (ICC) of 0.01. Regarding the assumption to reach a statistical power of 0.8 with a significance level of 0.05, the estimated number of participants needed to achieve study objectives is *n* = 252 (28 each shared accommodation in the clusters).

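### The printed sample-size inputs do not deliver the stated power of 0.8: the coefficient of variation is impossible as written, the 0.15 has no scale, and no within-person correlation or loss is given

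*Protocol article*

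**What the plan says.** All of the following comes from the protocol article.

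- Sample size {14} specifies "a stepped-wedge design with a cohort sample structure and an exchangeable correlation structure" and lists its numerical assumptions: "we assume a coefficient of variation of cluster sizes of 10 participants, mean difference of 0.15, and an intra-class correlation (ICC) of 0.01". The aim is "to reach a statistical power of 0.8 with a significance level of 0.05", and the result is 252 participants, 28 per accommodation.
- Outcomes {12} defines the primary outcome as refugees' knowledge on an adapted questionnaire, "creating a sum score for a continuous variable", measured at t0 to t3.
- Trial design {8} and Study setting {9} give nine accommodations, three in each of three sequences.
- The sections on retention {18b} and missing data {20c} foresee drop-out and missing values. The sample-size section makes no allowance for either.

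**The concern.** The section presents its listed assumptions as yielding 252 at power 0.8. One of them cannot be true as worded, because a CV is the SD divided by the mean and is not a number of participants. Another, the "mean difference of 0.15", cannot be interpreted without an SD or a statement that it is standardised.

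In a cohort stepped-wedge trial each person serves partly as their own control, so power depends strongly on the correlation between a person's repeated scores. The "an intra-class correlation (ICC) of 0.01" describes similarity between residents of one accommodation and does not supply that correlation.

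The power statement governs how a null primary result will be read. If the true power is well below 0.8, a null result could be taken as evidence of no benefit when the trial had limited ability to detect its own target effect.

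**Working it through.** **Inputs from the article.** Nine accommodations in three sequences of three; 28 per accommodation; four primary-outcome periods (t0 to t3); ICC 0.01; difference 0.15; alpha 0.05; target power 0.80.

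**Assumptions added because the article does not state them.** 0.15 is in SD units (SD = 1); the test is two-sided and normal; period effects are fixed; cluster autocorrelation is 1; there is no loss. IAC is varied.

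**Step 1: the plan's own figures.** 9 × 28 = 252, which agrees. The power of 0.80 cannot be reproduced from the printed inputs alone (step 3).

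**Step 2: the CV.** For n clusters the largest possible CV occurs when everyone is in one cluster, and equals √(n − 1). For nine clusters this is √8 = 2.83 (3.0 with the n − 1 form of the SD). A CV of 10 is therefore impossible. It may be a mislabelled SD of 10, giving 10/28 = 0.36, or it may mean 10%. At a total within-person correlation of 0.79, power is 0.793 with equal sizes, 0.793 with CV 0.1 and 0.787 with CV 0.36. The slip has little effect on power.

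**Step 3: power.** Write a = (1 − ICC)(1 − IAC)/28 for the part of the variance of an accommodation's period mean that is independent between periods, and b = ICC + (1 − ICC)·IAC/28 for the part shared across periods. The Hussey–Hughes closed form, with I = 9 and T = 4, is

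Var = I·a·(a + T·b) / [(IU − W)·a + (U² + ITU − TW − IV)·b].

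The design constants are U = 18, W = 126 and V = 42. Hence IU − W = 162 − 126 = 36, and U² + ITU − TW − IV = 324 + 648 − 504 − 378 = 90. Power = Φ(0.15/SE − 1.96).

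- IAC 0: a = 0.03536, b = 0.0100. Var = 9 × 0.03536 × 0.07536 / (1.2729 + 0.9000) = 0.01104, so SE = 0.105. Power = Φ(1.428 − 1.960) = 0.30.
- IAC 0.79: a = 0.00743, b = 0.03793. Var = 9 × 0.00743 × 0.15915 / (0.2673 + 3.4139) = 0.00289, so SE = 0.0538. Power = Φ(2.791 − 1.960) = 0.80.

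| IAC | SE | Power for 0.15 SD | Effect detectable at 80% power (2.80 × SE) |
|---|---|---|---|
| 0 | 0.105 | 0.30 | 0.29 SD |
| 0.5 | 0.081 | 0.46 | 0.23 SD |
| 0.7 | 0.064 | 0.65 | 0.18 SD |
| 0.79 | 0.054 | 0.80 | 0.15 SD |

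The exact threshold is IAC 0.792, a total within-person correlation of 0.01 + 0.99 × 0.792 = 0.794. With no within-person correlation beyond the ICC, power 0.80 would need 126 per accommodation (9 × 126 = 1134).

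**Step 4: how firm the threshold is.** Total within-person correlation needed for power 0.80, without loss:

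- base case: 0.794
- five periods: 0.771
- one-sided, four periods: 0.736
- one-sided, five periods: 0.708
- t test on 7 degrees of freedom: 0.850
- cluster autocorrelation 0.8: about 0.85

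The range is about 0.71 to 0.85.

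**Step 5: loss.** As a simple approximation, 20% loss is applied to every period, leaving 28 × 0.8 = 22.4 per accommodation. Power at the threshold IAC of 0.792 falls to about 0.71, and the IAC needed for 0.80 rises to 0.834. Loss that builds up gradually from t0 would cost somewhat less.

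**Step 6: readings that do reach 0.80 without loss.** With SD = 1, a total within-person correlation of 0.80 gives power 0.812, and 28 is then exactly the smallest sufficient size. An IAC of 0.80 gives 0.815. With 0.15 as a raw difference and SD 0.5, power is 0.81 at IAC 0 and 0.96 at IAC 0.5. With raw SDs of 2 to 5 and IAC 0.7, it is 0.22 to 0.07.

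**The case against.** The strongest reply has three parts.

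- **No error in 252 has been shown.** One round but unprinted value, a within-person correlation of 0.80, returns 28 per accommodation exactly. This stands. A reader might infer that the sample is too small, or that the trial has only an even chance of detecting its target. The documents support neither inference, because both need an SD and an IAC that are not given. Nor can 0.15 raw points be called negligible, since the items and range of the adapted scale are not stated.
- **The gaps are what a condensed article leaves to the full protocol.** This holds in part. A missing SD, IAC or loss allowance alone would be a matter of reporting detail. Here, though, the article lists assumptions and presents them as producing a stated power. One is impossible as worded, and the set does not yield that power without a further input on which the result depends heavily.
- **The CV slip is immaterial.** For power this is right under either plausible reading. It is still a wrong statement. A reader might take 0.36 as the intended value, but that is a guess and 10% is equally possible.

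**Conclusion.** The point holds as a defect in the stated justification. The printed inputs contain an impossible CV and do not deliver power 0.8. On the standardised reading, with the assumptions listed in the working, power runs from 0.30 to 0.65 for IAC from 0 to 0.7. It reaches 0.80 only at about 0.79, or a within-person correlation of about 0.71 to 0.85 across standard variants. With 20% loss, power at the base-case threshold is about 0.71.

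The missing scale and the missing within-person correlation are the material gaps; the CV is a factual error with little numerical consequence. Whether 252 is adequate cannot be settled from the article in either direction.

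**What to change.** Rewrite the sample-size paragraph to give:

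- the unitless CV actually used;
- whether 0.15 is standardised, or else its units and the SD of the sum score;
- the IAC assumed and its basis;
- whether the test is one- or two-sided;
- the expected loss by t3.

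Then re-run the calculation for 28 recruited per accommodation, net of that loss. If the supported inputs do not give 0.80, replace the claim "to reach a statistical power of 0.8" with the resulting power or the detectable effect, shown over a range of IAC.

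The cost is one paragraph and one re-run. Design, analysis and enrolment are unchanged. The downside is that the stated power may become less favourable.
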